#### Scale and questionnaire measurement

Anxiety and depression are the most prevalent mental illnesses contributing to the global infertility burden, which are also potential risk factors for IVF success. Emotional disorder can also lead to sleep problems and will influence the quality of life. Therefore, the scale and questionnaire measurement will be measured at baseline and on the trigger day to learn about changes in the mental disorder after the acupuncture treatments (**Table 4**). Self-rating anxiety scale (SAS) (29) and the self-rating depression scale (SDS) (30) are 20-item Likert scales, with raw scores that range from 20 to 80, which are converted to index scores by dividing the sum of the raw scores by 80 and multiplying by 100. Higher scores indicate greater severity of anxiety or depression symptomology. Index scores, 25–49 (raw scores 20–40); normal, 50–59 (raw scores 41–47); mild to moderate, 60–69 (raw scores 48–55); moderate to severe; and 70 and over (raw scores 56 and over), severe (31). The Pittsburgh Sleep Quality Index (PSQI) is a self-rated questionnaire to assess sleep quality and disturbance that can be used in clinical practice and research studies for patients with psychiatric or sleep problems and even among the general population (32). It contains 19 items in seven subdomains, including subjective sleep quality, sleep latency, sleep duration, habitual sleep efficiency sleep disturbances, use of sleeping medication, and daytime dysfunction (32). The sum scores of each item range daytime dysfunction from 0 to 21. The higher the patients’ scores, the worse sleep quality they experience. The fertile quality of life (FertiQoL) is an instrument to measure the quality of life in men and women experiencing fertility problems (33). FertiQoL consists of 36 items that assess core (24 items) treatment-related quality of life (QoL) (10 items) and overall life and physical health (two items). The items in the prototype FertiQoL survey were randomly presented and rated on a scale of 0–4, where higher scores indicated a more favorable quality of life.

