### Sample size

The purpose of this study was to evaluate the study’s feasibility and support the development of a future definitive RCT. Utilizing the upper confidence limit method, we determined that a pilot sample size of between 20 to 40 individuals can serve as a benchmark (34). Based on the consensus of the methodologists, statisticians, and acupuncturists, we decided that a sample size of 30 in each group (25) and a 20% estimated dropout rate were sufficient; thus, the total of 114 patients would be considerable (38 in each group).

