### Statistical analysis

Intention-to-treat (ITT) analysis encompassing all randomized patients will be conducted for all efficacy analyses. Additionally, a per-protocol (PP) analysis focusing on the primary outcome will be performed as a sensitive analysis, excluding patients who did not complete the acupuncture treatment. Missing outcome data will be complemented using multiple imputations with the package “Mice” from the R software (www.r-project.org).

Categorical variables will be reported by number and percentage, whereas continuous variables will be represented by mean and standard deviation (SD) (or median and interquartile range, IQR). The retention rate and treatment adherence will be reported in descriptive statistics.

For the primary outcome, CPR will be compared by the proportions of included patients with clinical pregnancy. To determine the independent factors, logistic regression will be used to identify baseline variables that are associated with outcomes. The retention rate and rates of biochemical pregnancy, ongoing pregnancy, blinding assessments, and adverse events will undergo statistical analysis using chi-squared tests or Fisher’s exact test. Other outcomes will be evaluated using one-way variance (ANOVA) models or Kruskal–Wallis analysis. The score of SAS, SDS, FertiQol, and PSQI, respectively, will be assessed at baseline and after treatment among groups on hCG trigger day. Statistical significance will be determined at *P <*0.05. Pairwise comparisons will be performed between the EA + IVF group and the pEA + IVF group and between the EA + IVF group and the IVF group in a *post hoc* analysis.

A predetermined subgroup analysis will be performed to determine whether the baseline characteristics (female age, ovarian stimulation protocol, etc.) affect the CPR to EA. The data was analyzed using SPSS version 27.0 (IBM, Armonk, NY, USA). As this is a pilot study, our results were considered exploratory.

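### SAS, SDS, FertiQoL and PSQI are compared by one-way methods that do not use the baseline score as a covariate: valid, but less precise than the data allow and open to chance imbalance

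*Protocol article*

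**What the plan says.** The Statistical analysis section of the protocol article assigns chi-squared or Fisher tests to a list of rates and then covers everything else in one sentence: "Other outcomes will be evaluated using one-way variance (ANOVA) models", with Kruskal–Wallis as the alternative. The four questionnaire scores are not in the list of rates, so they fall here. The next sentence says that these scores "will be assessed at baseline and after treatment among groups on hCG trigger day". It names no model of its own.

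The section on scales and questionnaires gives the purpose: "the scale and questionnaire measurement will be measured at baseline and on the trigger day to learn about changes in the mental disorder". Table 4 likewise gives each scale a baseline value and a trigger-day value. (Table 1 marks the second measurement under oocyte retrieval; either way there is one score before treatment and one after.)

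The only regression in the plan is for a different task: "logistic regression will be used to identify baseline variables that are associated with outcomes". Two arm contrasts are named as post hoc, EA against placebo EA and EA against IVF alone. The section ends by calling the results of this pilot exploratory.

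**The concern.** A one-way ANOVA has arm as its only term, and Kruskal–Wallis takes no covariate. A baseline score is collected for each scale, with the stated aim of learning about change, yet the named method does not adjust for it. Logistic regression cannot fill the gap for a continuous score.

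Two things are at stake. The first is precision: the part of the outcome variance that baseline explains stays in the error term. The second is chance imbalance. With about 30 women per arm, noticeable baseline differences between arms will be common, and a one-way comparison has no means of allowing for them. The reported questionnaire effects would be noisier than they need be.

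**Working it through.** **Inputs from the document.** 30 evaluable women per arm and 20% dropout (Sample size); 1:1:1 allocation; significance level 0.05, with sidedness not stated and two-sided assumed here.

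**The plan's own figure.** 30 / (1 − 0.20) = 37.5, rounded up to 38 per arm; 3 × 38 = 114. This reproduces the total in the Sample size section, so 30 per arm is the right number for what follows.

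**Assumptions.** The document gives no SD, effect size or baseline-to-post correlation r. I take r = 0.3, 0.5 and 0.7, equal SDs at the two time points and a common slope across arms, and work in SD units.

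**How often imbalance occurs.** The standard error of a baseline difference between two arms is √(2/30) = 0.258 SD, so 95% of chance differences lie within ±1.96 × 0.258 = ±0.51 SD. For a difference of 0.3 SD or more in either direction, 0.3 / 0.258 = 1.16, which has a two-sided probability of 0.245. If all 38 per arm were evaluable, the standard error would be 0.229 SD and the probability 0.191. These are per pair of arms and per scale.

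**What a 0.3 SD imbalance does.** The expected shift is r × 0.3 in a post-score contrast, (r − 1) × 0.3 in a change-score contrast, and 0 under ANCOVA.

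| r | Post score | Change score | ANCOVA |
|---|---|---|---|
| 0.3 | +0.09 SD | −0.21 SD | 0 |
| 0.5 | +0.15 SD | −0.15 SD | 0 |
| 0.7 | +0.21 SD | −0.09 SD | 0 |

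**Precision.** The text does not say whether the one-way test is run on the trigger-day score or on the change from baseline, so both are shown. The variance of an arm difference is proportional to 1 for the post score, 2(1 − r) for the change score and 1 − r² for ANCOVA. The ANCOVA ratio against the change score is (1 − r²) / [2(1 − r)] = (1 + r)/2.

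| r | ANCOVA / post score | Reduction | ANCOVA / change score | Reduction |
|---|---|---|---|---|
| 0.3 | 0.91 | 9% | 0.65 | 35% |
| 0.5 | 0.75 | 25% | 0.75 | 25% |
| 0.7 | 0.51 | 49% | 0.85 | 15% |

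Put in women: 30 per arm analysed on the post score alone give the precision of 30 × 0.91 = 27.3, 30 × 0.75 = 22.5 or 30 × 0.51 = 15.3 per arm under ANCOVA.

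**Power, as illustration.** For an assumed true pairwise difference of 0.5 SD with 30 per arm, power is 49.1% on the post score whatever r is. On the change score it is 37.3%, 49.1% and 70.5% for r = 0.3, 0.5 and 0.7, and under ANCOVA 52.8%, 60.9% and 77.4%.

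These figures are for comparisons of means. No corresponding gain was worked out for Kruskal–Wallis.

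**The case against.** The case for leaving the plan alone is substantial. Under randomisation the one-way test keeps its type I error and its estimate is unbiased over repeated randomisations. A reader might infer that the analysis is invalid or biased overall; it is not. Any bias is conditional on the imbalance that happens to arise. The scales are secondary outcomes, the trial is declared exploratory, and neither the primary outcome (clinical pregnancy rate) nor the pilot targets (recruitment, retention, attendance) depend on them. The size of the gain rests on an r that the document does not give; at r = 0.3 the gain over a post-score analysis is small. All of this stands, and it limits the weight of the point without removing it.

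Three stronger readings are tempting and do not hold:

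- That a baseline imbalance passes in full into the post-treatment contrast. The expected carry-over is only r times the imbalance.
- That the SDs handed on to a later trial are less precise. The marginal SD is the same whichever test is used. ANCOVA adds a residual SD, which is a different quantity.
- That significance tests of baseline scores are planned. The sentence saying that the scores "will be assessed at baseline and after treatment among groups on hCG trigger day" can be read as describing when they are measured, and it names no test.

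It may also be said that an unseen analysis plan could add covariates. That is possible, but the article does not leave the method open: it names one-way methods for these outcomes. If a change-score ANOVA was meant, ANCOVA is still the more precise for every r considered here.

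**Conclusion.** The point holds as an efficiency improvement to a valid analysis of exploratory secondary outcomes. ANCOVA is more precise than either one-way reading throughout r = 0.3 to 0.7. The saving in variance is between 9% and 49% if the post score was to be compared, and between 35% and 15% if the change was. The article does not settle which was intended, so neither set of figures can be quoted alone as the size of the loss. ANCOVA also removes the expected shift from a chance baseline difference, and at 30 per arm a difference of 0.3 SD or more should occur in roughly one trial in four for each pair of arms and scale. All of this rests on the assumed r, equal SDs and a common slope.

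**What to change.** In the Statistical analysis section, take the four questionnaires out of the general sentence on other outcomes. State that each trigger-day score will be analysed by ANCOVA with arm and the baseline score of the same scale as terms. Report adjusted mean differences with 95% confidence intervals for EA against placebo EA and EA against IVF alone. Name a rank-based or robust version for use if residuals are clearly non-normal. Say that baseline scores will be reported descriptively by arm.

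The cost is a change of wording and one degree of freedom per model. No further data, visits or participants are needed, and SPSS, which the plan already names, fits the model.

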## Discussion

Recurrent IVF failure significantly impairs the patients’ quality of life and leads to a great economic burden for the families as well as society. This parallel, three-arm, randomized, placebo-controlled trial will assess the feasibility of acupuncture in treating infertile women who will undergo IVF.

This trial meets the methodological demand for adequate randomization, allocation concealment, and blinding of patients, outcome assessors, and statisticians. In this study design, there are several factors different from previous studies. Firstly, three treatment sessions per week during the ovarian stimulation and at least five sessions will be considerable. Previous studies conducted two before embryo transfer (8, 35), or one session was added on the 6–8 days of ovarian stimulation (three sessions in total) (9, 36). In these trials, the dose of acupuncture was far from adequate. In our previous meta-research, a high dosage of treatment showed better results for pregnancy outcomes. As a CAM, EA aims to improve the quality of the oocyte; enough dosage acupuncture will be needed as Magarelli (16) and White (37) have suggested. Secondly, EA with 2/100 Hz will be administered during the ovarian stimulation. In 1996, Stener-Victorin (38) found that EA can reduce the blood flow impedance in the uterine arteries. It is suggested that both of these effects are due to a central inhibition of the sympathetic activity. Moreover, Stener-Victorin reported that EA inhibits hyperactivity in the sympathetic nervous system in influencing ovarian morphology (39). For the tensity of electro-acupuncture, low tensity with 2–50 Hz was utilized frequently, especially in TEAS. However, low density and high tensity alternately will be more beneficial for long-duration treatment. Thus, this study is designed using EA with 2/100 Hz. Thirdly, acupoints were summarized from bibliographic retrieval. In total, 87 studies of acupuncture in treating infertility were screened and subjected to quality assessment. We ranked the acupoints with a high frequency utilized. CV12 (*Zhongwan*), ST25 (*Tianshu*), CV 6 (*Qihai*), CV4 (*Guanyuan*), KI12(*Dahe*), EX-CA1 (*Zigong*), SP10 (*Xuehai*), ST36 (*Zusanli*), SP6 (*Sanyinjiao*), LR3 (*Taichong*), BL23 (*Shenshu*), BL32 (*Ciliao*), and KI3 (*Taixi*) were recommended by 34 professors from all over the world. To our knowledge, CV 6 (*Qihai*), CV4 (*Guanyuan*), KI12 (*Dahe*), and EX-CA1 (*Zigong*) are positioned around nerves, which are connected with the ovaries and uterus (40). Blood vessels will be stimulated by nerve control. Moreover, the ovarian and uterus functions are governed by the hypothalamic–pituitary–ovarian (H–P–O) axis. Relaxing the depression and anxiety and improving the quality of life and sleep, the H–P–O axis might be influenced by stimulation. However, the placebo effect of EA cannot be ignored. We set a pEA in our pilot research; non-penetration of skin and blunt needles will be utilized to minimize the effect. To blind the patients successfully, we treated them separately and avoided communications.

There are certain limitations to consider. Firstly, due to the inherent nature of acupuncture, it is impractical to blind either the acupuncturists or the patients during the treatment process when comparing the EA + IVF group with the IVF control group. Secondly, our study was confined to a single-center trial involving 118 patients, potentially introducing selection bias. Nevertheless, for future trials, we aim to recruit patients from multiple centers in a significantly larger sample size to mitigate these limitations.

### Trial status

This study is currently in the recruitment phase. The first patient was randomized on August 15, 2023, and the study is expected to end in the middle of 2024.

## Ethics statement

The studies involving humans were approved by Sichuan Jinxin Xi’nan Women and Children Hospital. The studies were conducted in accordance with the local legislation and institutional requirements. The participants provided their written informed consent to participate in this study. Written informed consent was obtained from the individual(s) for the publication of any potentially identifiable images or data included in this article.
